### Inclusion Criteria

Participants will be included if they meet the following criteria:

The Mini International Neuropsychiatric Interview (MINI version 5.0) will be used to identify subthreshold depression patients who have depressive symptoms but do not meet the major depression disorder criteria according to the Diagnostic and Statistical Manual of Mental Disorders (Fifth Edition) (DSM-V);Aged between 18 and 60 years;The score of HAMD-17:7 ≤ HAMD <17;No treatment related to depression has been received in the past 2 weeks;Antibiotics, probiotics, yogurt, and other fermented dairy products were not taken before random sampling;Voluntarily participating in this trial with a written informed consent form.

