### Sample Size Estimation

This pilot study aims to assess the efficacy of acupuncture for subthreshold depression as well as the feasibility of a further large clinical trial. The HAMD-17 was used as the main effect indicator to calculate the required sample size. According to relevant published literature (19, 20), the difference in HAMD-17 scores between the acupuncture and placebo groups was 4.87, and the standard deviation was 1.99 in the acupuncture group and 7.18 in the placebo group. Group sample sizes of 27 and 27 achieve 90.75% power to reject the null hypothesis of equal means and with a significance level (alpha) of 0.050 using a two-sided two-sample unequal-variance *t* test by PASS 15 software. Assuming a dropout rate of 15%, 64 participants are necessary, with 32 participants in each group.

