#### Primary Outcome Measurement

The primary outcome will measure changes in the HAMD-17 scores between baseline and 8 weeks after randomization. The Hamilton Depression scale (22), developed by [name] in 1960, is a widely used depression scale. It includes cognitive impairment, block, despair, anxiety/somatization, sleep disorder, weight, and diurnal changes. It is mainly used to evaluate the severity of depressive symptoms in adult patients with depression and the curative effect before and after clinical trials. The higher the score, the more serious the degree of depression.

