#### Secondary Outcomes

##### HAMD-17 at Other Timepoints

The primary outcome measurement is the HAMD-17 at week 8 after randomization; however, it will also be used at weeks 4 and 20 after randomization.

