### Statistical Analyses

R 4.0.5 software will be used for statistical analysis by an independent statistician who will not participate in the study. Two-tailed *p*-values < 0.05 will be considered statistically significant. Normally distributed continuous variables will be presented using the means and standard deviation, and non-normal variables will be presented as the medians and interquartile range. All efficacy analyses will be performed using the intent-to-treat (ITT). Missing data will be replaced according to the principle of the last observation carried forward method (28). The per-protocol (PP) population will be analyzed to determine the consistency of the results. The data before and after treatment in each group will be compared based on a paired *t* test or Wilcoxon signed-rank test, and the comparison between groups will be performed using an independent sample *t* test or Mann–Whitney *U* test. Categorical variables will be analyzed using the χ^2^ test or Fisher's exact test. For comparisons of the primary outcomes across the groups, we will use analysis of covariance with the baseline HAMD-17 to adjust. A generalized linear mixed model will be used for repeated measures, setting group and time as fixed factors and patient as a random factor; the interaction effects of group^*^time will be included in the model.

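### The repeated-measures model names patient as its one random factor; fitted as written it assumes equal variance and equal correlation across visits, which can miscalibrate the visit-specific group contrasts

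*Protocol article*

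**What the plan says.** The Statistical Analyses section of the protocol article describes the repeated-measures analysis in one sentence: "A generalized linear mixed model will be used for repeated measures, setting group and time as fixed factors and patient as a random factor". A group-by-time term is also in the model. No residual covariance structure is named, and the text does not say whether baseline is one of the levels of time.

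The primary comparison is a separate analysis: "For comparisons of the primary outcomes across the groups, we will use analysis of covariance with the baseline HAMD-17 to adjust". Its endpoint is defined under Primary Outcome Measurement: "The primary outcome will measure changes in the HAMD-17 scores between baseline and 8 weeks after randomization".

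Three other places bear on the variance pattern:

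- Inclusion Criteria: "The score of HAMD-17:7 ≤ HAMD <17".
- HAMD-17 at Other Timepoints, on the scale beyond the primary visit: "it will also be used at weeks 4 and 20 after randomization".
- Sample Size Estimation: "the standard deviation was 1.99 in the acupuncture group and 7.18 in the placebo group".

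**The concern.** A single random patient effect with independent, equal-variance residuals implies compound symmetry: the same variance at every visit, and the same correlation between any two visits. This design strains both parts. Entry truncates HAMD-17 at baseline only, so spread can grow afterwards. The visits are 4, 4 and 12 weeks apart, and the last gap follows the end of the 8-week course, so equal correlations are not something to count on.

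If the assumptions fail, the model applies an average variance to every visit. Group differences read from it then have standard errors that are too large where spread is below average (early) and too small where it is above average (late). A 95% interval or 5% test at week 20, the only HAMD-17 assessment after treatment ends, would not have its stated coverage or level.

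**Working it through.** **The plan's own figure.** SE = √((1.99² + 7.18²)/27) = √(55.51/27) = 1.434. The noncentrality is 4.87/1.434 = 3.40 with 29.97 Satterthwaite df, which gives 90.75% power as stated. 27/0.85 = 31.8, hence 32 per arm and 64 in total. The sample size reproduces and does not depend on the mixed model.

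**Inputs from the document.** Baseline range 7–16; visits at 0, 4, 8 and 20 weeks; n = 32 per arm. Integers spread evenly over 7–16 have SD 2.87; the largest possible population SD in that range is (16 − 7)/2 = 4.5. The root mean square of the two planning SDs is √((1.99² + 7.18²)/2) = 5.27.

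**Assumptions.** All visit-specific SDs and correlations below. Using 5.27 as a follow-up SD is also an assumption.

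**Formulas.** Take complete visits, which single imputation would produce. Let v̄ be the mean visit variance, c̄ the mean between-visit covariance, σⱼ² the true variance at visit j and σ₀ⱼ its covariance with baseline. The ratio r of model SE to true SE is:

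- group difference at visit j: r = √(v̄/σⱼ²)
- group difference in change from baseline: r = √(2(v̄ − c̄)/(σ₀² + σⱼ² − 2σ₀ⱼ))

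The actual type I error is about 2[1 − Φ(1.96 r)].

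**Differences at a visit, baseline included as a level of time.** With SDs 2.87/4/5.27/5.27, the variances are 8.24, 16, 27.77 and 27.77, so v̄ = 19.95.

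- Week 4: r = √(19.95/16) = 1.12, error 2.9%.
- Weeks 8 and 20: r = √(19.95/27.77) = 0.85, error 9.7%.

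Other assumed spreads:

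| SDs at weeks 0/4/8/20 | week 4 | week 8 | week 20 |
|---|---|---|---|
| 2.87/3/3.5/4 | 2.8% | 5.9% | 9.8% |
| 2.5/4/5/6 | 2.5% | 7.4% | 13.6% |
| all equal | 5% | 5% | 5% |

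**Week-8 change contrast.** Take SDs 2.87 at baseline and 5.27 at all follow-ups, so v̄ = 22.89.

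- All correlations 0.5: c̄ = (7.56 + 13.89)/2 = 10.72. The model uses 2(22.89 − 10.72) = 24.3; the truth is 8.24 + 27.77 − 15.12 = 20.9. r = 1.08, error 3.4%.
- Baseline–follow-up 0.3, follow-up–follow-up 0.8: c̄ = (4.54 + 22.22)/2 = 13.38. The model uses 19.0; the truth is 8.24 + 27.77 − 9.07 = 26.9. r = 0.84, error 10.0%.

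Simulation with 20,000 null trials per setting agrees. With arm SDs of 1.99 and 7.18 at follow-up instead, the simulated error is 8.0% (correlations 0.3/0.7), 10.1% (0.3/0.8), 7.2% (0.5/0.7), 9.3% (0.5/0.8) and 4.0% (0.5/0.5). A test using the contrast's own variance stays near 5% throughout.

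**Baseline left out of the model.** With follow-up SDs 4/5.27/5.27, v̄ = (16 + 27.77 + 27.77)/3 = 23.85, and the errors are 1.7%, 6.9% and 6.9%. With 4/5/6 they are 1.3%, 4.7% and 9.8%.

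**Overall group-by-time F test.** In simulation over these patterns it rejects in about 5–7% of null trials.

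**The case against.** The other side has several fair points, and most of them stand as limits on the claim.

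- The sentence does not say that patient is the only random term, and a random patient effect does not exclude a structured residual covariance. A condensed article may leave that to the analysis plan. This stands as a caution, but the article does write down a model, and an analyst who fits what is written gets compound symmetry.
- The planning SDs are not tied to a visit, nor identified as endpoint or change scores, and 1.99 lies below the illustrative baseline SD of 2.87. A reader might infer that the design contradicts the model's assumptions. The document does not show this: it gives no variance or correlation by visit, so the assumptions may fail, not must.
- The direction of the error depends on assumed correlations. At 0.5 throughout, the week-8 change test is conservative.
- The text assigns no visit-specific contrasts to this model. It names t or rank tests for between-group comparisons and ANCOVA for the primary. For the interaction, the effect the text does name, the disturbance is small.
- The truncation argument is strongest if baseline is a level of time, which is not stated. Without baseline, the week-8 error is near nominal to moderate and week 20 is the main exposure.

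A reader might also infer that the trial's main p-value is at risk. It is not: the primary week-8 result comes from the separate ANCOVA.

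**Conclusion.** The point holds in conditional form and for the secondary repeated-measures analysis only. As written, the model assumes equal variances and equal correlations that this design gives reason to doubt. Under the assumed SDs and correlations, a nominal 5% visit-specific contrast has a true error of about 1–4% in the conservative settings and about 7–13% at weeks 8 and 20 in the unfavourable ones; the strongest widening tried comes to just under 14%. If variances and correlations are in fact equal, nothing is wrong. To say outright that the model's p-values are wrong would go further than the document allows. The change is still worth making, because it is a standard method, costs little and removes the dependence on an assumption nobody can check before the data are in.

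**What to change.** In Statistical Analyses, for the continuous repeated outcomes, replace the random-patient term with wording such as: time as a categorical factor, group, group by time, and an unstructured within-patient covariance with a separate variance at each visit, fitted by REML with Satterthwaite or Kenward-Roger degrees of freedom. If it does not converge, use a simpler heterogeneous structure with a sandwich variance. Report the week-4, week-8 and week-20 group differences with 95% confidence intervals from this model, and say whether baseline is a response or a covariate. A covariance that differs by arm is optional: it answers the unequal planning SDs, which are a separate matter.

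The cost is a sentence or two of text and a few lines of R, settled before group labels are opened. With four visits the covariance has 4 + 6 = 10 parameters instead of 2, which 64 patients should normally support, and late-visit intervals will usually be slightly wider.

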### Quality Control

To ensure the smooth progress of the research, before the formal start of the clinical trial, we will hold special clinical training to unify the clinical researchers. We will focus on the implementation plan of the project and the standard operating procedures so that each clinical researcher is familiar with the research process and specific implementation details, to improve the consistency of internal observation and the consistency between observers and ensure the reliability of clinical research conclusions. To reduce the withdrawal of patients, we will improve and maintain patients' good compliance and urge patients to stick to the treatment as much as possible during the study. All dropout subjects will be asked to state their reason, and these reasons will be analyzed.

Only researchers participating in clinical trials may have access to the subjects' personal medical records, and they will sign the investigator's statement or confidentiality commitment to include confidential content. The ethics committee has the right to inspect clinical trial records. Data will be processed in an anonymized way, and information that can identify the subject's individual identity will be omitted.

## Discussion

There is a lack of clear diagnostic criteria for subthreshold depression in the ICD-10 and the DSM-V. Thus, subthreshold depression is mainly diagnosed with identification tools for the diagnosis of depression, such as the MINI-International Neuropsychiatric Interview and HAMD-17. As a special critical state of disease, subthreshold depression has a significantly higher risk of transforming into depressive disorder than the general population (29). Compared with healthy people, people with a low level of education, low social support, history of serious chronic diseases, poor health, greater stress in the past 6 months, and living in poverty were more likely to suffer from subthreshold depression (30). Early intervention can relieve symptoms, reduce the risk of severe depression, and prevent progression to other adverse consequences. However, the current evidence does not support the use of drugs to intervene in patients with subthreshold depression (11, 12). Psychotherapy, such as cognitive behavioral therapy (CBT), is the main method to intervene in subthreshold depression at present (31, 32). The economic cost of patients receiving CBT intervention is still high, and the standardization and consistency of CBT intervention vary greatly among different centers (33). Acupuncture, as a safe non-drug therapy, has the advantages of simple operation and low treatment cost. It has been widely used to treat different psychiatric conditions, including depressive disorder (14, 15, 34). To date, few studies have investigated acupuncture for subthreshold depression (18, 35). The main principles for the treatment of depression in the theory of traditional Chinese medicine are tranquilize the mind and disperse stagnated hepatoqi. GV20, GV29, and HT7 will be used to tranquilize the mind, and LR3, ST25, and ST36 to disperse stagnated hepatoqi.

The goal of this RCT is to assess the effectiveness of acupuncture compared with minimal acupuncture to prove whether there is a placebo effect for subthreshold depression. In addition, the gut-brain axis plays an important role in depression (36, 37). However, there is no evidence that acupuncture interferes with subthreshold depression through the gut-brain axis; therefore, we will collect blood and stool samples from the subjects to establish a biological sample bank. If our clinical trials prove that acupuncture in the treatment of subthreshold depression is not just a placebo, we will use this biological sample bank to explore the mechanism of acupuncture for subthreshold depression.

The primary limitation of our trial is that acupuncturists cannot be blinded. Second, as a preliminary exploratory study, this study was designed as a single center study. If the study is effective, we will conduct further multicenter research.

## Trial Status

The protocol version is 2.0 (in July 22, 2021.) The trails have begun on July 26, 2021 and approximately completed on July 26, 2022.

## Ethics Statement

All participants must grant written informed consent once trial details are fully presented. The authors are accountable for all aspects of work, ensuring that questions related to accuracy or integrity of any part are appropriately investigated and resolved. The ethical approval (2021-055-KY) was given by the Institutional Review Board (IRB) of Affiliated Hospital of Shandong University of Traditional Chinese Medicine.

## Abbreviations

MDD: major depressive disorder
DSM: Diagnostic and Statistical Manual of Mental Disorders
EA: electroacupuncture
CBT: cognitive behavioral therapy
HAMD-17: Hamilton Depression Scale-17
CES-D: Center for Epidemiologic Depression scale
PHQ-9: The 9-item Patient Health Questionnaire
GAD-7: 7-item Generalized Anxiety Disorder
SF-12v2: SF-12v2 Health Survey
VAS: visual analog scale.
